## **37. BROAD PROJECT AIMS**

4.1. To establish the immune response in the serum and bronchoalveolar lavage (BAL) as measured cross-sectionally and longitudinally during the three year post-LTx and the association with later episodes of acute rejection or the subsequent development of CLAD.

4.2. To determine whether episodes of viral, fungal or bacterial infection in the LTx recipient trigger further increases in the secretion of these biomarkers and thus act as an inflammatory stimulus.

## **38. BACKGROUND**

### **5.1 The immune response to lung transplantation**

Successful outcomes following LTx depend on our ability to pharmacologically manipulate the immune system to prevent rejection of the lung allograft. The antigens involved in graft rejection are encoded by the major histocompatibility complex (MHC). This group of highly polymorphic genes defines the human leukocyte antigens (HLA) which are expressed on virtually all cell surfaces. The polymorphic nature of these allopeptides defines the genetic signature of each individual and allows the host immune system to differentiate between self and foreign peptides. The majority of transplanted lung allografts are MHC-mismatched to the recipient. As such, the transplanted lung will be seen as foreign to the recipient's immune system. This leads to activation of immune pathways that if left unchecked would lead to rejection and destruction of the newly transplanted lung. We are interested in whether structural differences between transplant recipients and their donors, termed eplets, may drive the acute cellular and humoral rejection responses following LTx.

### **5.2 Chronic Lung Allograft Dysfunction**

LTx chronic rejection has been described pathologically as Obliterative Bronchiolitis (OB) and physiologically as airflow limitation, in the form of the Bronchiolitis Obliterans Syndrome (BOS). However, increasingly other phenotypes of chronic rejection have been recognized, in particular the Restrictive Allograft Syndrome (RAS), characterized by restrictive physiology, interstitial infiltrates on radiology, and interstitial fibrosis, acute fibrinoid organizing pneumonia (AFOP) and diffuse alveolar damage (DAD) on histology (REF). To encompass these important emerging variants and concepts of chronic dysfunction, the term Chronic Lung Allograft Dysfunction (CLAD) has recently been created. We have been interested to see whether structural differences between transplant recipients and their donors may drive immune responses that lead to the later development of CLAD. Historically, the degree of matching between a transplant recipient and donor has been determined by counting the number of mismatched HLA-A, B and DR antigens of the donor. HLA antigens have multiple epitopes that can be recognised by specific antibodies. Elucidation of the three-dimensional molecular structures and amino acid sequence differences between HLA antigens allows structural characterisation of HLA antigens, and what are termed eplets. We have recently demonstrated that HLA matching at the eplet level protects against CLAD (7).

### **5.3 Acute Rejection**

Despite the use of maintenance immunosuppression, acute cellular rejection is a common problem post lung transplant with 34% of adult LTx recipients experiencing at least one episode during the first year

post-transplant. The lung allograft is particularly susceptible to alloreactivity with the incidence of acute rejection being higher following LTx compared to other solid organ transplants. Whilst the direct effects of acute rejection are usually controlled and reversed following high-dose intravenous steroid treatment, the indirect effects remain problematic, with episodes of acute rejection being strongly associated with the later development of chronic lung allograft dysfunction (CLAD). Given the need for invasive transbronchial biopsies to provide a histological diagnosis of acute cellular rejection, we have previously evaluated biomarkers in the blood and BAL and their association with acute rejection (2-5). Functional assays of T cell and B cell function in the blood may identify patients at higher risk of acute cellular rejection. Analysis of the BAL is very useful in providing mechanistic insights into the immunology of graft function and rejection following LTx. However, BAL findings seen in acute rejection must be interpreted in the context of those described in stable lung transplant recipients, and after taking into account the confounding nature of chronic airway infection.

#### **5.4 Infection in immunosuppressed lung transplant recipients**

Infection is commonly encountered following LTx and is largely related to the use of immunosuppressive medication. We have a long-standing interest in how opportunistic infections such as CMV (8) and Aspergillus (9) have both direct effects on the lung allograft, as well as indirect effects through an association with CLAD. The airways, historically thought to be sterile, are now known to harbor a microbiota that changes in its constituents depending upon the health status of an individual. This lung microbiome consists of bacteria, viruses and fungi, which are in intimate contact with cells in the lung providing tonic stimuli to our immune system. As is routine clinical practice, the current study will also include a detailed prospective analysis of infections, and associated risk factors in the cohort of LTx recipients. In particular, we will determine the impact and interaction of bacteria, viruses and fungi in the transplanted lung, in order to inform improved treatment and prevention of CLAD.

### **39. STUDY PROPOSAL**

LTx saves lives, however the long-term viability of the allograft is limited by the immune response to it and the development of CLAD. The production of *de novo* anti-HLA alloreactive donor-specific antibodies (DSA) is deleterious to the graft and is associated with CLAD. However, the immune cell response following LTx and its relationship to the lung microbiome is poorly understood. We propose a thorough and integrated delineation of the immune response to LTx. We will obtain a comprehensive picture of the lower airway bacterial, viral and fungal communities in LTx recipients, and determine the implications of the lung microbiome on inflammation, lung tissue remodelling pathways and allograft function. Following LTx, we will have defined immune and physiological biomarkers of rejection that will better inform the use of appropriately focused immunosuppressive therapies with a

view to reducing CLAD and prolonging survival following LTx. Insights gained will extend beyond LTx to all types of solid organ transplantation.

#### **40. RESEARCH PLAN**

##### **Specific Aim #1: Defining HLA eplet mismatch scores**

**Rationale:** The humoral antibody-antigen immune response describes the interaction between anti-HLA DSA with the cognate non-self HLA molecule expressed within the lung allograft. HLA genes are highly polymorphic with over 10,000 HLA Class I and II alleles. Anti-HLA antibodies recognise specific exposed regions of the HLA antigen that consist of chains of amino acid sequence located within the complement determining regions, termed eplets.. Approximately 600 HLA Class I and II eplets have been described by Duquesnoy *et al.* (10) using the theoretical computer algorithm HLAMatchmaker. Functional eplets specifically recognise HLA antibodies and are exposed within the binding groove demonstrating antigenicity, i.e. reactivity with antibody, and immunogenicity, i.e. ability to elicit immune response. LTx recipients are transplanted with HLA-mismatched donor lungs. HLA typing will be performed by Luminex sequence-specific oligonucleotide or sequenced-based typing for HLA-A, -B, -C, -DR and -DQ (Victorian Transplantation and Immunogenetics Service). The HLAMatchmaker 500 pair (ABC and DRDQ eplet) program will be used as a research tool to assess eplet matching for all LTx (<http://www.hlamatchmaker.net/>). The calculated linear score of structural diversity for each LTx will be used for the subsequent studies looking at the impact of structural incompatibility on immune pathways and allograft dysfunction.

##### **Specific Aim #2: Immune response in high eplet mismatch lung transplant recipients**

###### **x) *De novo DSA production***

**Rationale:** Anti-HLA DSA may be present at the time of LTx (sensitised recipient) or develop *de novo* following LTx, and may be specific to HLA-class I and/or HLA Class II. The alloreactivity of DSA is determined by whether they are bound within the lung allograft, and whether they amplify an immune response. The C1q assay is a modification of the standard Luminex assay that distinguishes complement-fixing (and therefore injurious) from non-complement-fixing DSA. The clinical utility of the C1q assay has been demonstrated in renal transplantation, and similar studies are awaited in LTx. DSA can also be alloreactive via complement-independent pathways. NK cells and macrophages can be directly activated via the low-affinity Fc receptor resulting in antibody-independent cell-mediated cytotoxicity. Aim #2 will integrate DSA results with eplet mismatch scores and other immune markers to provide a comprehensive description of Antibody Mediated Rejection (AMR).

###### **xi) *B-cell specificity, phenotype and function***

**Rationale:** B cells can be alloreactive, either as precursors (naïve or memory B cells) of DSA-producing plasma cells or as antigen-presenting cells to allospecific T-cells. HLA tetramers provide an opportunity to track antigen-specific B cell responses longitudinally from the time of LTx. In LTx, the dynamics

and role of alloreactive B cells in producing anti-HLA DSA and graft dysfunction has not been described.

B cell subtypes will be phenotyped from the blood of LTx recipients by flow cytometry in the lab of [name] of immune cells will be assessed using a stimulated intracellular cytokine stain. The dynamics of B and T cell biology will be tracked longitudinally over the first 12 months, and will be correlated with eplet mismatch scores and *de novo* DSA production (assessed at 3 and 12 months post-transplant).

**xii) *Antibody-dependent NK cell cytotoxicity***

**Rationale:** The complement-independent mechanisms that lead to AMR are poorly understood, although recent work suggests that NK cells may be important effectors of Antibody-Dependent Cell-Mediated Cytotoxicity (ADCC). We have previously shown that NK cells are activated in LTx recipients and contribute to DSA-mediated allograft injury (5). Molecular signatures from allograft biopsies support the alloreactive potential of NK cells. We aim to use an *in vitro* NK-cell ADCC assay to analyse the role of DSAs in promoting NK cell activation. NK cells will be identified by flow cytometry (CD3-CD56+ lymphocytes) in the blood LTx patients at 3 and 12 months post-transplant.

**Specific Aim #3: Determine the immunological profiles of the lower airways of lung transplant recipients**

We will characterise the immunological environment of the lower airways of LTx recipients at each timepoint (i.e. 2 weeks, 3, 6, 9, 12 and 18 months) by RNAseq of immune cells isolated from the lavage fluid. We will perform Mass Spectrometry of the lavage fluid to characterise the metabolome, lipidome and proteome. Bioinformatic integration of these datasets (see Aim 5) will allow us to gain deep insight into the immunological profiles of the patient groups.

**Specific Aim #4: Identification of the bacterial, fungal and viral communities in lung transplant recipients**

*Bacterial and fungal community identification:* Fungal and bacterial DNA will be amplified and sequenced. The virome will be characterised, using two experimental approaches in order to ensure we capture a complete and informative dataset. First, PCR amplification will be used to analyse the total set of BAL samples informing on the carriage of a specific set of RNA and DNA viruses, including a panel of anelloviruses which we hypothesize will be highly relevant in the lung transplant setting. In a second step, we will refine the patient pool for analysis based upon the clinical, immunological, bacterial, fungal and viral PCR results and perform metagenomic sequencing providing us with in-depth unbiased data on viral carriage.

**Specific Aim #5: Bioinformatics and integration of microbial, immunological and clinical datasets**

Network-based approaches have emerged as a powerful way to study microbial systems and analyse high-dimensional datasets. Using the bacterial, fungal and viral sequencing datasets, we will construct and combine ecological networks using dissimilarity and correlation-based methods. This will firstly allow us to determine the extent to which bacterial, fungal and viral communities are connected by causal relationships, and in particular, we can identify “key-stone” species which would be predicted to play a major role in community dynamics and consequently the immunological and health status of the transplant recipient.

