**42. INCLUSION/EXCLUSION CRITERIA**

Approximately 150 patients, including 10-15 single lung transplant recipients, will be enrolled at The Alfred Hospital

Inclusion Criteria

- Adults  $\geq 18$  years of age
- Lung Transplant Recipients
- Provide Written Consent

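### Aim 5 claims causal relationships from correlation and dissimilarity networks, and the viral sequencing that feeds them comes from a patient pool chosen on the very results the networks link

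*Supplement*

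**What the plan says.** All references are to protocol version 4.0 in the Supplement.

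- **Specific Aim #5, method and data.** The inputs are introduced as "Using the bacterial, fungal and viral sequencing datasets", and the method is "we will construct and combine ecological networks using dissimilarity and correlation-based methods".
- **Specific Aim #5, target.** The networks are then said to "determine the extent to which bacterial, fungal and viral communities are connected by causal relationships". They are also to identify key-stone species that "would be predicted to play a major role in community dynamics and consequently the immunological and health status of the transplant recipient".
- **Specific Aim #4, viral data.** There are two steps. In the first, "PCR amplification will be used to analyse the total set of BAL samples", for a set list of viruses. In the second, "we will refine the patient pool for analysis based upon the clinical, immunological, bacterial, fungal and viral PCR results", and then "perform metagenomic sequencing providing us with in-depth unbiased data on viral carriage". No rule, number or probability of selection is given. No patient selection is stated for bacterial or fungal sequencing.
- **Section 42, size.** "Approximately 150 patients, including 10-15 single lung transplant recipients, will be enrolled at The Alfred Hospital".
- **Section 43, Analysis.** This covers chi-square, t, Mann-Whitney and Cox analyses. Confounder adjustment appears only with the Cox models for acute rejection and CLAD. Nothing is stated for the networks.

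**The concern.** There are two separate problems.

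**Target and method do not match.** An undirected edge says that two taxa vary together across samples. It does not separate a direct effect from a shared cause. Immunosuppression, antimicrobials, infection and time since transplant could all move bacteria, fungi and viruses together. The protocol's own background (5.3) warns that lavage findings in acute rejection are confounded by chronic airway infection, but this caution is not carried into Aim 5.

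**The viral layer is selected on the variables to be linked.** Aim 5 draws on viral sequencing data, and the only viral sequencing described is the metagenomic step. Its pool is chosen on the same domains that the networks then connect. Two features that are independent in the cohort can become correlated among the patients kept, because selection depends on both.

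At stake is the reading of the result. Edges produced by shared causes or by selection could be reported as causal, and key-stone taxa named from them could be tied to recipients' health. Viral carriage in the chosen pool could also be taken for carriage in the cohort.

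**Working it through.** The plan states no edge threshold, error rate or sample size for the networks, so there is no figure of its own to reproduce. The checks below show what the stated methods would do. N = 150 comes from section 42 and the two-sided 0.05 level from section 43. Applying that level to edges is an assumption, as are all other settings.

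**1. Shared cause, whole cohort, no selection.** Let X and Y each load b on one common factor, with no direct link. Their correlation is ρ = b². The edge is declared with probability of about Φ(t − 1.96), where t = atanh(ρ)·√(150 − 3).

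| b | ρ | t | approximate edge rate | simulated (3,000 runs) |
|---|---|---|---|---|
| 0.3 | 0.09 | 1.09 | 19% | 20% |
| 0.5 | 0.25 | 3.10 | 87% | 88% |
| 0.7 | 0.49 | 6.50 | 100% | 100% |

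The test is right to find association here. The error lies in calling it causal.

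**2. Selection on both features.** Let X and Y be independent standard normal, and let the selection score be S = √(R²/2)·(X + Y) + √(1 − R²)·noise. R² is the share of the score that the two features explain. Keep the top fraction p, so n = 150p. With z the upper-p normal quantile, λ = φ(z)/p and k = λ(λ − z), truncation gives

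r = −a/(1 − a), where a = (R²/2)·k.

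The values of k are 0.781 (p = 0.20), 0.722 (p = 0.33) and 0.637 (p = 0.50). Worked example for p = 0.33 and R² = 0.5: a = 0.25 × 0.722 = 0.180, r = −0.180/0.820 = −0.22. With n = 50, t = atanh(0.22)·√47 = 1.53, so the edge rate is about Φ(1.53 − 1.96) = 33%.

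| p (n) | R² | induced r | approximate false-edge rate | simulated (3,000 runs) |
|---|---|---|---|---|
| 0.20 (30) | 0.25 | −0.11 | 9% | 9.4% |
| 0.33 (50) | 0.25 | −0.10 | 10% | 11.3% |
| 0.50 (75) | 0.25 | −0.09 | 11% | 11.5% |
| 0.20 (30) | 0.50 | −0.24 | 25% | 26.6% |
| 0.33 (50) | 0.50 | −0.22 | 33% | 35.3% |
| 0.50 (75) | 0.50 | −0.19 | 37% | 37.1% |

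At R² = 1, where the two features alone decide selection, the simulated rate is 96-99%. That is a limiting case, not an expectation.

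**3. Selection on one feature only.** If S depends on X alone, X and Y stay independent among those kept. The simulated rate is 4.5%, so there is no inflation.

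**4. Where selection reaches.** It reaches the edges computed in the metagenomic pool. It does not reach the viral PCR panel, which covers all lavage samples, nor bacterial or fungal sequencing, for which no selection is stated.

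**The case against.** The strongest reply is that Aim 5 is exploratory. Key-stone species are only predicted to matter, and the acute rejection and CLAD analyses in section 43 do not depend on the networks. That limits the consequence and it stands. It does not rescue the sentence on causal relationships, which carries no such hedge and is corrected nowhere else in version 4.0.

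On selection, the reply is that the size depends on a rule the plan does not state and may be nil. This also stands. The right statement is that selection can create false edges, not that it must. The stated criteria do, however, span all the domains to be linked. The description of the metagenomic data as unbiased may refer to untargeted sequencing, in contrast to a fixed PCR panel, so it is not in itself a false claim. Even on that reading, carriage in a pool chosen on results is not cohort carriage.

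Two stronger readings are tempting, and the documents do not support them:

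- **Raw proportions will be correlated, so compositional artefact will fill the networks.** The plan does not say so, and its wording leaves room for composition-aware correlation. The size also depends heavily on assumptions. With independent taxa at n = 100 and one taxon about 20-fold dominant, Spearman tests on proportions flag about 64%, 32% and 10% of pairs for 10, 20 and 50 taxa, but only about 5-6% at 100-200 taxa. With no dominant taxon the rate is about 5-9% for 10 to 50 taxa. If the kingdoms are normalised separately, independent taxa in different kingdoms stay independent.
- **Serial samples will be pooled as if independent.** The plan is silent on this, and Aim 3 speaks of profiles at each timepoint.

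Both are points to specify, not demonstrated errors.

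**Conclusion.** The concern holds in two parts.

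1. The causal claim in Aim 5 cannot be met by the methods named. This rests on the text alone and needs no simulation.
2. The result-dependent metagenomic pool can add false links and does not represent the cohort. Under the assumed linear selection score, with 20-50% of 150 patients kept, the false-edge rate is about 10% at R² = 0.25 and about 25-38% at R² = 0.50, against 5%. There is almost no inflation if only one of the two features drives selection. The effect is confined to the viral metagenomic layer.

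Following the text as written would lead to a wrong conclusion about causation, so this is more than missing detail. The main association and Cox analyses of acute rejection and CLAD are untouched.

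**What to change.** - **Claim.** In Aim 5, replace causal relationships with associations, and describe key-stone taxa as hypotheses for later testing.
- **Metagenomic subset.** Draw it at random within strata of the selection variables, give every stratum a non-zero recorded probability, and weight analyses by the inverse. Alternatively, keep the selected pool for description and limit cohort-level cross-kingdom statements to the unselected data: bacterial and fungal sequencing, and viral PCR on all lavage samples.
- **Repeated samples.** Build networks per timepoint, or use a within-patient model.
- **Advisable.** Name a composition-aware correlation method, so that the question does not arise.

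The change is mainly one of wording and sampling procedure, and the number of samples sequenced can stay the same. The cost is a more modest claim and, if weights are used, somewhat lower precision.

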#### **Specific Aim #6: Applying microarray to describe the molecular phenotype of lung allografts**

The current standard of biopsy-based assessment of lung transplants is the ISHLT histology classification applied to transbronchial biopsies. This assessment is based largely on empirical classifications and expert opinions, and provides little insight into the pathophysiological and immunological drivers of CLAD. Microarray analysis establishes diagnostic patterns of abnormality (and normality), but as yet is not been rigorously applied in the LTx setting.

We will utilise Microarray Analysis at 3 and 12 months post-transplant, scores provided by the Molecular Microscope Diagnostic System used to guide diagnosis of T cell mediated rejection and AMR will be applied to the lung allograft biopsies provided. These Microarray results will be correlated with eplet mismatch scores and immune markers and CLAD.

#### **SUB-STUDY: Single Lung Transplant (SLTx) Recipients**

From January 2021, the study will continue to recruit only participants who receive a single lung transplant. We will perform Specific Aims 3-5 above, on the lavage fluid from both the transplanted lobe and the native lobe. The datasets generated from the different lobes will be compared in order to ascertain whether the immunological and microbiological characteristics of the transplanted lobe develops independently, or in parallel, with the native lobes. This analysis will inform whether the local microenvironmental changes within individual lobes influence the health trajectory of transplant recipients.

## **41. METHODOLOGY**

### **8.1 Patient Recruitment:**

All adult patients undergoing lung transplantation, and whose long-term follow-up will be at the Alfred Hospital will be invited to participate in the study. Patients would be enrolled prior to transplantation.

